**A58. What are the secondary outcome measures?(if any)**

Precision assessment of dual energy X-ray absorptiometry

**A59. What is the sample size for the research? How many participants/samples/data records do you plan to study in**

*total? If there is more than one group, please give further details below.*

Total UK sample size: 62

Total international sample size (including UK):

Total in European Economic Area:

*Further details:*

PART A: 20 males and 20 females

PART B: 22 females

**A60. How was the sample size decided upon?** *If a formal sample size calculation was used, indicate how this was done, giving sufficient information to justify and reproduce the calculation.*

PART A: A statistical power analysis was conducted. It was determined that a sample size of 8 per group was required to have 80% power to detect a between-group difference in muscle strength of 14%, when using a dependent t-test with a 0.05 two-sided significance level. A ~20% drop-out is anticipated, therefore, 10 males and 10 females in both groups will be recruited (n = 40 total).

PART B: A statistical power analysis was conducted. It was determined that a sample size of 9 per group was required to have 80% power to detect a between-group difference in muscle strength of 13%, when using a dependent t-test with a 0.05 two-sided significance level. A ~20% drop-out is anticipated, therefore, a total of 22 females will be recruited.

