There is evidence to suggest that males and females may respond differently to resistance exercise, with respect to muscle damage. For instance, some studies have shown greater and more sustained increases in blood markers of muscle damage and inflammation in males than females following resistance exercise (Amorim et al., 2014; Heavens et al., 2014). It has been speculated whether these differences are due to a protective effect of oestrogens (Enns & Tiidus, 2008; Peter M Tiidus, 2003). Therefore, not only is the muscle damage response to heavy vs. lighter resistance exercise inconsistent in males, but it cannot be determined whether females will respond in the same way. Thus, the first objective (part a) of this research is to compare the muscle damage response induced by an acute bout of high- or low- load resistance exercise between males and females.

Another strategy that has shown to reduce exercise-induced muscle damage is the consumption of dietary protein, either as a whole-food source (such as milk) or as a supplement (such as isolated whey protein). It is believed that protein, or rather the amino acids which make up protein, aid the repair or replacement of damaged muscle fibres, then promote growth of the new healthy fibres. Accordingly, research has shown that ingesting protein/amino acids before or after muscle-damaging exercise can alleviate muscle soreness, improve blood markers of muscle damage, and reduce the decline in maximal force and flexibility. In particular, studies have shown that consuming a ~20 g dose of milk protein immediately after (Cockburn et al., 2008) or for several times a day after (Draganidis et al., 2017) resistance exercise improved the recovery time of muscle soreness and maximum force, and also lowered levels of damage markers in the blood. However, these studies were conducted with male participants who were well-trained in resistance exercise. It is not yet known whether milk protein effectively reduces exercise-induced muscle damage in untrained females. Therefore, the second objective (part b) of this research is to investigate the impact of milk protein ingestion on exercise-induced muscle damage in untrained females.

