**A61. Will participants be allocated to groups at random?**

☒ Yes ☐ No

*If yes, please give details of the intended method of randomisation:*

With each eligible participant identified, a coin will be tossed to decide which group they go into.

**A62. Please describe the methods of analysis (statistical or other appropriate methods, e.g. for qualitative research) by which the data will be evaluated to meet the study objectives.**

PART A: The Shapiro Wilk test will be used to assess the distribution of the data and to ensure no assumptions for statistical models are violated. Any data that violate the assumptions will be logarithmically transformed before statistical analysis. A two-way mixed design analysis of variance (ANOVA) will be used to analyse each muscle damage marker between exercise conditions and within time points. A two-way between-subjects ANOVA will be used to analyse each muscle damage marker between exercise conditions and between sexes. Independent t tests with Bonferroni corrections will be used to compare time-points between exercise conditions for all measures. Paired t tests will be used to detect any significant within-group changes between time points.

PART B: The Shapiro Wilk test will be used to assess the distribution of the data and to ensure no assumptions for statistical models are violated. Any data that violate the assumptions will be logarithmically transformed before statistical analysis. A two-way mixed design ANOVA will be used to analyse each muscle damage marker between dietary conditions (protein or placebo) and within time points. Independent t tests with Bonferroni corrections will be used to compare time-points between dietary conditions for all measures. Paired t tests will be used to detect any significant within-group changes between time points.

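### Part A's 80% power is for one sex-by-load cell against another, by a paired test; A62 names no such comparison, and the load-by-sex interaction falls short of 80% for the same 14 points

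*Protocol*

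**What the plan says.** Protocol A60 (Part A) states: "It was determined that a sample size of 8 per group was required to have 80% power to detect a between-group difference in muscle strength". The difference is put at 14%. The test is described in these words: "when using a dependent t-test with a 0.05 two-sided significance level". It gives no SD, SD of differences or correlation. It continues: "A ~20% drop-out is anticipated, therefore, 10 males and 10 females in both groups will be recruited (n = 40 total").

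A13 describes Part A as a randomised parallel-group study in which the low-load (30% 1RM) and high-load (80% 1RM) groups each hold equal numbers of males and females.

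For Part A, A62 lists:
- a mixed ANOVA of load by time;
- a two-way ANOVA: "A two-way between-subjects ANOVA will be used to analyse each muscle damage marker between exercise conditions and between sexes";
- Bonferroni-corrected independent t tests between loads, not split by sex;
- paired t tests for change within groups.

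Objective 1 (A10) concerns sex differences in the damage response to heavy or lighter loads. A12 notes that findings on heavy versus lighter loads are inconsistent in males and that "it cannot be determined whether females will respond in the same way".

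**The concern.** A power statement should describe a test that the analysis section runs. Here it appears to describe a contrast between two of the four sex-by-load cells, while A62 names only pooled comparisons and a factorial ANOVA. Part A therefore has one power figure and no named test to which it belongs.

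The error runs in both directions. A pooled contrast uses twice as many people per side as the comparison that was sized, so it has more power than a cell contrast with the same SD. The load-by-sex interaction is a difference between two cell differences, so it has less. A reader who attached the 80% to the question of whether females respond to load as males do could take a non-significant interaction as fair evidence that they do.

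The sentence has a second fault. A dependent t-test analyses paired observations, and people in different parallel groups are not paired. With no SD or correlation given, this leaves the true power of every Part A comparison undetermined.

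**Working it through.** **Inputs.** From A60: 8 per group, 80% power, 14% difference, two-sided alpha 0.05, dependent t-test, about 20% drop-out, 40 recruited. No SD is given, so 8 cannot be reproduced; the effect size that it implies can be back-solved.

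**Step 1: what a group is.** 8/0.8 = 10. A60 recruits 10 males and 10 females at each load: 4 cells x 10 = 40. Had a group meant a whole load arm, the total would have been 2 x 10 = 20. The sized unit is one cell.

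**Step 2: variance of the contrasts**, with n per cell and common SD s.
- Cell v cell: 2s²/n.
- Pooled load or sex contrast (2n v 2n): 2s²/(2n) = s²/n.
- Interaction, (female high − female low) − (male high − male low): 4s²/n, twice the cell contrast. This holds whatever s is.

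**Step 3: the 80% taken as an unpaired 8 v 8 test** (noncentral t).
- Cell contrast: ncp = d·sqrt(n/2), df = 2n − 2 = 14. Power 0.80 needs d = 1.507, so s = 14/1.507 = 9.3 points.
- Interaction of 14 points: ncp = d/sqrt(4/n), df = 4n − 4. At n = 8, ncp = 1.507/0.707 = 2.13, df 28, power 53.9%. At n = 10, ncp = 1.507/0.632 = 2.38, df 36, power 64.0%.
- Interaction detectable with 80% power at 8 per cell: 2.052 SD, and 2.052 x 9.29 = 19.1 points.
- Pooled load or sex contrast of 14 points (16 v 16): about 98%, before any Bonferroni correction.
- Because n is rounded up, 8 is the minimum for any d from 1.507 to 1.632. Over that range interaction power is 54% to 61% at 8 per cell and 64% to 71% at 10. With the normal-approximation d = 1.401 it is 48% and 58%.

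**Step 4: the 80% taken from the dependent test as named.** ncp = dz·sqrt(n), df = n − 1 = 7. With 8 pairs, power 0.80 needs dz = 1.156, an SD of differences of 14/1.156 = 12.1 points. To move to unpaired data a pair correlation rho must be assumed: d = dz·sqrt(2(1 − rho)).

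| assumed rho | d | unpaired 8 v 8 | interaction, 8 per cell | interaction, 10 per cell | pooled contrast, 8 per cell, before Bonferroni |
|---|---|---|---|---|---|
| 0 | 1.635 | 86% | 61% | 71% | 99% |
| 0.3 | 1.368 | 72% | 46% | 56% | 96% |
| 0.5 | 1.156 | 58% | 35% | 43% | 88% |
| 0.7 | 0.895 | 39% | 23% | 28% | 69% |

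The rho = 0.5 row is the same as using 12.1 points directly as the between-person SD. The detectable interaction is then 2.052 x 12.1 = about 25 points.

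**Step 5: most favourable variant examined.** dz at the top of its rounding range (1.273) with rho = 0 gives interaction power of 69% at 8 per cell and 79% at 10. No variant examined reaches 80%.

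**The case against.** **The 54% is not a property of the plan.** This stands. It needs an unpaired test, while A60 names a paired one and gives no SD. It also needs exactly 8 completers in each cell, which allocation by coin toss (A61) does not by itself ensure. The figure must be given with its conditions and the range beside it. The direction does not depend on them: the doubled variance needs no SD.

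**The interaction need not be the question.** A reader might infer that Part A asks only about the interaction. The documents do not support that. Objective 1, and the aim that closes the same discussion in A12, can also be read as males against females at each load, which is a cell contrast. The interaction is the natural test of the gap A12 describes and one reasonable reading of Objective 1, not the only one.

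**Follow-up tests of the two-way ANOVA could compare cells.** They could, and such detail is often left to an SAP, which is not at hand. So it is too strong to say that no cell comparison will ever be made. What can be said is that A62 names none.

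**A60 never calls 14 points an interaction.** True; applying it there is a choice. It is the only Part A effect size given, and a smaller interaction would have less power still.

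**Nothing says a null interaction would be read as equality, or claims 80% for it.** Also true. The risk arises because 80% is the only Part A figure on offer.

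**Conclusion.** The concern holds in this form: A60's power is for one cell against another, obtained with a test for paired data and no stated SD, and it corresponds to no comparison that A62 names. It cannot be carried over to a 14-point load-by-sex interaction.

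Interaction power is about 54% at 8 completers per cell (64% at 10) if the 80% is for an unpaired 8 v 8 test. It is about 35% to 61% at 8 per cell if the 80% came from the dependent test with pair correlation 0.5 to 0, and lower at higher correlations. All these figures assume a common SD and equal cells.

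Two stronger readings should be resisted. One is that Part A is underpowered throughout: under the unpaired assumption the pooled contrasts have about 98% before Bonferroni, although 69% is possible at a pair correlation of 0.7. The other is that the arithmetic from 8 to 40 is wrong: the inflation to 10 per cell checks. The defect is a power statement that does not match the analysis.

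**What to change.** Keep n = 40 and revise the Part A text of A60:
1. State the SD of the strength measure and its source.
2. Replace the dependent t-test with the unpaired tests that A62 runs.
3. Restate power at 8 completers per cell (32 in all), separately for the pooled load and sex contrasts, allowing for Bonferroni where A62 applies it, and for the load-by-sex interaction.
4. Give the interaction detectable with 80% power. As a guide until the SD is supplied, this is about 19 points under the unpaired assumption and about 25 if 12.1 points is the between-person SD. The sponsor should compute the final figures from its own SD rather than adopt these.
5. State that the interaction will be reported with its confidence interval, and that a non-significant result will not be read as equal responses in the sexes.

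The cost is wording and one recalculation, with no extra participants. The stated power for the sex-by-load question will be less favourable than the single 80% suggests.

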**A13. Please summarise your design and methodology. It should be clear exactly what will happen to the research participant, how many times and in what order. Please complete this section in language comprehensible to the lay person. Do not simply reproduce or refer to the protocol. Further guidance is available in the guidance notes.**

OBJECTIVE 1/PART A: This study will employ a randomised parallel groups design, for which 40 healthy participants (20 males and 20 females) aged 18-35 years will be recruited. Prior to the first laboratory visit, prospective participants will have the opportunity to ask questions and gain further information about the study via a video/phone call with the

lead researcher. If willing to participate, participants will be asked to electronically sign a consent form. Female participants will be asked to record their menstrual cycle and inform the lead researcher at the onset of menses – this information will be used to arrange the time of the baseline assessments, as all measures will be conducted during the late follicular phase of the menstrual cycle.

For the first visit, which acts as a familiarisation session, participants will arrive at the laboratory in the morning and be screened for eligibility with a standard health and readiness to exercise questionnaire. Next, participants will be familiarised with the exercise equipment and demonstrated correct form. Then, participants' maximal strength will be estimated through a one repetition maximum (1RM) test on the leg press and leg extension machines. Approximately three days later, participants will return to the laboratory and a baseline assessment of body composition will be conducted using dual energy X-ray absorptiometry (DXA). Two whole-body DXA scans will be conducted in each participant (one immediately following the other after repositioning) to allow for the precision of DXA to be measured. The 1RM test will be repeated on the leg press and leg extension machines for confirmation of maximal strength. Participants will then be randomly assigned to either a low-load (30% 1RM) or high-load (80% 1RM) exercise condition, such that each group will have an equal number of males and females.

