Immediately following the exercise bout (post), another venous blood sample will be taken (3 x 8.5-10 mL) and the measures of limb circumference, range of motion, and muscle soreness will be repeated. Then, participants will be provided a dairy yoghurt containing 20 g of milk protein to stimulate muscle repair and growth. These four measures (excluding protein consumption) will be repeated during the morning of visits four (+24 h), five (+48 h), six (+72 h), and seven (+168 h). Also, during visits six and seven, the 1RM strength test will be repeated on the leg press and leg extension. Over the experimental period, a total of 171 mL of blood will be collected from each participant. This is the equivalent of ~34 teaspoons and is a common amount obtained during exercise physiology research. The blood samples will be used to analyse serum concentrations of creatine kinase, myoglobin (markers of muscle damage), C-reactive protein, and interleukin-6 (markers of inflammation).

**OBJECTIVE 2/PART B:** This study will employ a randomised parallel groups design, for which 22 healthy females aged 18-35 years will be recruited. Prior to the first laboratory visit, prospective participants will have the opportunity to ask questions and gain further information about the study via a video/phone call with the lead researcher. If willing to participate, participants will be asked to electronically sign a consent form. Participants will be asked to record their menstrual cycle and inform the lead researcher at the onset of menses – this information will be used to arrange the time of the baseline assessments, as all measures will be conducted during the late follicular phase of the menstrual cycle.

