For the first visit, which acts as a familiarisation session, participants will arrive at the laboratory in the morning and be screened for eligibility with a standard health and readiness to exercise questionnaire. Next, participants will be familiarised with the exercise equipment and demonstrated correct form. Then, participants' maximal strength will be estimated through a one repetition maximum (1RM) test on the leg press and leg extension machines. Approximately three days later, participants will return to the laboratory and a baseline assessment of body composition will be conducted using dual energy X-ray absorptiometry (DXA). The 1RM test will be repeated on the leg press and leg extension machines for confirmation of maximal strength. Participants will then be randomly assigned to either a protein or placebo group. The protein group will be consuming a whole-food source of milk protein (dairy yoghurt) providing 20 g of milk protein and the placebo group will consume a carbohydrate-based food source that contains the

same amount of calories.

Visit three will occur three weeks later. In between visits two and three, participants will be asked to record their habitual diet and activity for three days, which will be used to assess any between-group differences. For each subsequent assessment day, participants will be prescribed a standardised breakfast that will contain either the protein or placebo product to consume at home 3 hours prior to attending the laboratory. Participants will consume one dose of their allocated supplement in the laboratory after exercise and be given a further two doses to consume at home interspaced by four hours. Therefore, 4 doses of the supplement will be consumed in each 24-hour period for four consecutive days, though on the final testing day, only one dose will be consumed with breakfast (17 doses total). Otherwise, participants will be instructed to consume their habitual diet, and during each laboratory visit a 24-hour dietary recall will be conducted to assess any changes and between-group differences in dietary intake. Participants will also be instructed to abstain from the use of non-steroidal anti-inflammatory drugs, strenuous exercise, engagement in massage or cryotherapy, and the consumption of alcohol, additional protein supplements, vitamin and mineral supplements, and ergogenic aids during the study period.

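### Both sample sizes are calculated for a dependent t-test although both parts compare separate randomised groups, so the stated 80% power is unsupported, most clearly in Part B

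*Protocol*

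**What the plan says.** **Sample size (Protocol A60).** Part A takes 8 per group to give "80% power to detect a between-group difference in muscle strength of 14%, when using a dependent t-test". Part B takes 9 per group to give "80% power to detect a between-group difference in muscle strength of 13%, when using a dependent t-test". Both use a two-sided 0.05 level. Allowing for about 20% dropout, Part A recruits 10 males and 10 females per load group (40 in total) and Part B recruits 22 females. No SD, SD of differences or correlation is stated.

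**Design (Protocol A13).** Part A: "This study will employ a randomised parallel groups design", and "Participants will then be randomly assigned to either a low-load (30% 1RM) or high-load (80% 1RM) exercise condition". Part B: "This study will employ a randomised parallel groups design, for which 22 healthy females aged 18-35 years will be recruited", and "Participants will then be randomly assigned to either a protein or placebo group". Nobody receives both conditions, and no matching is described.

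**Analysis (Protocol A62).** Part A: "Independent t tests with Bonferroni corrections will be used to compare time-points between exercise conditions for all measures". Part B has the same plan for the two dietary conditions. Both parts also have a mixed ANOVA (condition by time), and Part A adds a between-subjects ANOVA of condition and sex. Paired t-tests are reserved for change over time within a group.

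**The concern.** A dependent t-test needs two linked measurements, usually from the same person. Its error term is the SD of the within-pair difference, from which stable between-person variation has dropped out. A comparison of two separate groups keeps that variation. A number of pairs that gives 80% power therefore does not in general give 80% power when used as the number per independent group. A60 describes the effect as a difference between groups and then names a test that cannot assess one in this design, and A62 names a different test.

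A60 is the only justification for the numbers recruited, and its form asks for enough information to reproduce the calculation. If milk protein shows no effect in Part B, that result will be read against an 80% power for which the protocol gives no basis.

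**Working it through.** **Inputs from the protocol.** A60: n = 8 with a 14% difference, n = 9 with a 13% difference, 80% power, two-sided alpha 0.05, recruitment of 10 per sex-by-load cell and 22 in total. A13: strength is retested at visits six and seven, so there are two post-exercise strength time points.

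**Inputs not given.** The SD and the within-pair correlation ρ. Values of ρ below are assumptions. Equal group sizes are also assumed.

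**Step 1: the plan's own figure.** It cannot be reproduced forwards without an SD, so it is solved backwards. Paired power is P(T > t₀.₉₇₅,ₙ₋₁), where T is non-central t with n − 1 df and non-centrality dz·√n.
- Part A: critical t (7 df) 2.365; non-centrality for 80% is 3.270; dz = 3.270/√8 = 1.156; SD of differences = 14/1.156 = 12.1 points.
- Part B: critical t (8 df) 2.306; non-centrality for 80% is 3.201; dz = 3.201/√9 = 1.067; SD of differences = 13/1.067 = 12.2 points.

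These are minimum effects. If 8 and 9 are the smallest adequate numbers, dz lies between 1.156 and 1.273 in Part A and between 1.067 and 1.156 in Part B. The upper ends are the values at which 7 and 8 pairs would already suffice.

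**Step 2: the same effect in an independent t-test, Part B.** Since SD of differences = SD·√(2(1 − ρ)), the two-sample effect is d = dz·√(2(1 − ρ)). The test has 2n − 2 df and non-centrality d·√(n/2). At ρ = 0.5, d = 1.067, non-centrality = 1.067 × √4.5 = 2.263 and critical t (16 df) = 2.120, which gives 57% power.

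| Assumed ρ (dz = 1.067) | d | SD (points) | Power, 9 v 9 |
|---|---|---|---|
| 0 | 1.509 | 8.6 | 85% |
| 0.25 | 1.307 | 9.9 | 74% |
| 0.5 | 1.067 | 12.2 | 57% |
| 0.75 | 0.754 | 17.2 | 32.5% |

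At ρ = 0.5 the upper dz of 1.156 gives 63%, so the range at that correlation is 57-63%. With no dropout (11 v 11), the minimum dz gives 66%. An independent t-test at 9 v 9 needs d = 1.407 for 80%. At an SD of 12.18 that is a difference of 1.407 × 12.18 = 17.1 points, not 13.

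**Step 3: if 'dependent' is a slip for 'independent', Part B.** Then SD = 13/1.407 = 9.2 points, and power is 80% at alpha 0.05. With Bonferroni for the two post-exercise strength time points (alpha 0.05/2 = 0.025) it is about 69%. A62 does not state the number of comparisons, so two is an assumption.

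**Step 4: Part A.** Recruiting 10 per sex in each load group to retain 8 makes 8 the number per sex-by-load cell.
- Load within one sex, 8 v 8, ρ = 0.5: non-centrality = 1.156 × √4 = 2.312; critical t (14 df) = 2.145; power 58%. At dz = 1.273 it is 66%.
- Load pooled over sex, 16 v 16, SD 12.1: non-centrality = 1.156 × √8 = 3.270 with 30 df; power 89%, or 81% at alpha 0.025.
- The same contrast at SD 14/1.507 = 9.3 (the slip case): 98%.
- The sex main effect is also 16 v 16 and, for a difference of the same size, has the same power.
- The pooled figures assume the same SD after pooling. At ρ = 0.75 (SD 17.1) the pooled contrast falls to 61%.

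**The case against.** **'Dependent' may be a slip of the pen.** This is plausible, because A60 speaks of a between-group difference and A62 uses independent tests. If so, 80% holds at alpha 0.05 with an SD of about 9.2-9.3 points. The same wording appears for both parts, however, and without an SD nobody can check which test was run. The text needs correcting either way.

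**The loss of power depends on an assumed correlation.** This stands. A reader might infer that the trial has less than 80% power. The protocol does not support that, because at correlation 0 independent-test power is 85% in Part B.

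**Part A has reserve.** This stands too. A reader might take 58% as the power of Part A, but A62's t-test between exercise conditions is not split by sex, so it compares 16 with 16. Nor is load the only contrast with that reserve, since the sex main effect has it as well.

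**The sex-by-load interaction.** A reader might infer that Objective 1 fails for lack of power on the interaction. A10 can be read that way, but it can also be read as asking for sex differences under either load. The 14% in A60 is a between-group difference, not an interaction. An interaction power would rest on an effect size that the protocol never states.

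**Bonferroni.** A62 attaches it to the t-tests only and states no reduced alpha for the ANOVAs. It is therefore too strong to say that 0.05 will not be used anywhere.

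**Conclusion.** The concern holds as a mismatch between the sample-size test and the design. In both parts A60 names a paired test for a comparison of separate groups, contrary to A13 and A62, and omits the SD needed to reproduce 8 or 9. The stated 80% is unsupported for the planned comparison; the protocol does not show whether it is met or missed.

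The consequence is clearest in Part B, which has no pooled contrast to fall back on. Its power is about 57-63% at an assumed correlation of 0.5, and lower or higher as the correlation rises or falls. In Part A the doubt concerns load comparisons within one sex, at about 58-66% under the same assumption. The pooled load contrast and the sex main effect keep 89-98% for SDs from 12.1 to 9.3 points, and 81% or more with Bonferroni for two time points.

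**What to change.** Rewrite A60 for two independent groups. State the SD of the strength outcome and its source, and use the alpha and the contrast that A62 will apply, including the number of comparisons behind the Bonferroni correction. Keep 40 and 22 participants and report whichever follows, the power or the difference detectable with 80% power. If 'dependent' is a slip, correct it and give the SD that produced 8 and 9.

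For Part A, say whether 8 per group refers to the comparison pooled over sex or to the comparison within each sex. If the sex-by-load interaction is a target, state its power separately.

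The 57-58% powers and the 17% detectable difference are illustrations under an assumed correlation and should not be copied into A60. The new figures must come from a sourced SD.

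The cost is a rewording and a rerun of the calculation. No extra participants are needed, but the stated figure may be less favourable.

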Upon arriving at the laboratory for the third visit (pre), a trained phlebotomist will collect a venous blood sample in three vacutainers; one containing a serum separator (8.5 mL); and two containing no reagent (10 mL) (28.5 mL total). Following blood collection, the participants' limb circumference of the thigh will be measured with a standard measuring tape and their limb range of motion will be assessed with a goniometer. Muscle soreness will be measured by use of a visual analogue scale (VAS) questionnaire while performing a standard bodyweight squat, and the pressure-pain threshold (PPT) test using a standard pressure algometer. Participants will then perform a single bout of resistance exercise, firstly on the leg press and secondly, on the leg extension, separated by five-minutes rest. The exercise protocol will consist of a warm-up set (10 repetitions at 50% of the participants pre-established 1RM), followed by three sets performed to volitional failure (when a full repetition can no longer be completed) at 80% 1RM. Two-minutes of rest will be awarded between each set of exercise and the participants will be verbally encouraged throughout.

Immediately following the exercise bout (post), another venous blood sample will be taken (3 x 8.5-10 mL) and the measures of limb circumference, range of motion, and muscle soreness will be repeated. Then, participants will consume their allocated dietary supplement (protein or placebo). These procedures will be repeated during the morning of visits four (+24 h), five (+48 h), six (+72 h), and seven (+168 h). Also, during visits six and seven, the 1RM strength test will be repeated on the leg press and leg extension. Over the experimental period, a total of 171 mL of blood will be collected from each participant. This is the equivalent of ~34 teaspoons and is a common amount obtained during exercise physiology research. The blood samples will be used to analyse serum concentrations of creatine kinase, myoglobin (markers of muscle damage), C-reactive protein, and interleukin-6 (markers of inflammation).

**A14-1. In which aspects of the research process have you actively involved, or will you involve, patients, service users, and/or their carers, or members of the public?**

- ☐ Design of the research
- ☐ Management of the research
- ☐ Undertaking the research
- ☐ Analysis of results
- ☐ Dissemination of findings
- ☒ None of the above

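### Part B is sized on a strength t test at an unadjusted two-sided 0.05 (A60), but A62 Bonferroni-corrects the between-diet t tests for every measure, so the stated 80% power does not apply to the corrected strength test.

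*Protocol*

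**What the plan says.** **Sample size (Protocol A60, Part B).** The aim is put as "to detect a between-group difference in muscle strength of 13%, when using a dependent t-test with a 0.05 two-sided significance level"; the size given for this is 9 in each arm, at a power of 80%. The answer mentions no multiplicity adjustment and gives no SD or standardised effect. It does not say which time point or machine the 13% refers to. Drop-out is added afterwards: "A ~20% drop-out is anticipated, therefore, a total of 22 females will be recruited".

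**Analysis (Protocol A62, Part B).** The first model is an ANOVA: "A two-way mixed design ANOVA will be used to analyse each muscle damage marker between dietary conditions (protein or placebo) and within time points". The pairwise between-group tests follow: "Independent t tests with Bonferroni corrections will be used to compare time-points between dietary conditions for all measures". The number of comparisons in the correction is not given.

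**Schedule (Protocol A13, Part B).** Strength is measured as 1RM at familiarisation and again at visit two, before exercise. Afterwards, "during visits six and seven, the 1RM strength test will be repeated on the leg press and leg extension", that is, at +72 h and +168 h. Blood markers, soreness, range of motion and circumference are taken at six times: pre, post, +24, +48, +72 and +168 h.

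**The concern.** A60 and A62 attach different significance levels to the between-diet t test on strength. The calculation spends the whole 0.05 on one comparison. The analysis divides 0.05 over several and includes strength in that rule. A smaller alpha at the same sample size means less power, so the 80% given to the ethics committee describes a test that A62 does not carry out at that level.

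This is separate from A60's use of a dependent t test for two parallel groups. Changing that word to independent would leave 0.05 in one answer and 0.05 divided by at least two in the other.

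**Working it through.** **Inputs.** From A60 (Part B): 9 per group, 80% power, two-sided 0.05, a difference of 13%. From A62: independent t tests with Bonferroni correction, divisor k not stated. From A13: strength at two post-exercise times, plus a baseline, on two machines.

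**Can the 9 per group be reproduced?** No, because no SD is given. The effect is therefore solved from A60's own claim, assuming an independent t test.

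**Method.** With n per group, df = 2n − 2 and noncentrality λ = d × √(n/2). Power is P(T > t_crit), where T is noncentral t(df, λ) and t_crit is the 1 − α/2 quantile of t(df). The opposite tail is negligible.

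**Step 1. Effect implied by A60.** With n = 9, df = 16 and α = 0.05, t_crit = 2.120. Power of 0.800 needs λ = 2.985, so d = 2.985/√4.5 = 1.407. The implied SD is 13/1.407 = 9.24 percentage points.

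**Step 2. Same n and d at α = 0.05/k.**

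| k | What it would count for strength | α | t_crit | Power |
|---|---|---|---|---|
| 1 | as A60 assumes | 0.05 | 2.120 | 80.0% |
| 2 | +72 h and +168 h | 0.025 | 2.473 | 69.4% |
| 3 | those two and baseline | 0.0167 | 2.673 | 62.6% |
| 4 | two post-exercise times × two machines | 0.0125 | 2.813 | 57.7% |
| 6 | three times × two machines, or the six times of the other measures applied to strength | 0.0083 | 3.008 | 50.9% |

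**Step 3. Sensitivity to the test assumed.** A literal dependent t test with 9 pairs (standardised difference 1.067 for 80% at 0.05) gives 67%, 59%, 53% and 45% for k = 2, 3, 4 and 6. The normal approximation (d = 1.321) gives 71%, 66%, 62% and 57%. Every variant is below 80% for every k of 2 or more.

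**Step 4. Would the 22 recruited cover it?** If nobody dropped out and the split were equal, 11 per group at d = 1.407 would give 80% at k = 2, 75% at k = 3, 71% at k = 4 and 65% at k = 6. A60 sets that margin aside for drop-out of about 20%.

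**Step 5. Part A.** A62 compares exercise loads with the sexes pooled. Eight per sex-and-load cell is then 16 per load. Solving A60's Part A claim in the same way (8 per group) gives d = 1.507. If pooling leaves that effect unchanged, power with 16 per load is 98% at 0.05, 97% at k = 2 and 95% at k = 3. The loss there is small.

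**The case against.** **The divisor is unknown.** This stands. A54 says that a statistical analysis plan was reviewed, and the family for the correction may be defined there. No single corrected power can therefore be read off the protocol. A reader might infer from the table that true power is 51%. The documents do not support that: strength is not measured at six time points, and k = 6 needs either both machines with baseline included or a divisor borrowed from the other measures. It remains true that a correction over strength's own times has a divisor of at least 2.

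**The effect is back-solved.** This stands too. The percentages hold only if the 80% is right for an independent t test. If A60 really computed a paired test, power of the independent test at an unadjusted 0.05 would already be about 85%, 74% or 57% for assumed correlations of 0, 0.25 or 0.5. That error could outweigh the loss from Bonferroni. It changes the percentages, not the mismatch of alphas.

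**The ANOVA comes first, and the t tests are follow-up.** A62 does not make the t tests conditional on the ANOVA, and A60 bases the sample size on a t test. The between-group t test in A62 is the one that carries the correction.

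**A60 sets no rule for success.** This is correct. A reader might infer that a strength result with p = 0.03 is positive by A60 and negative by A62. A60 sizes the trial and states no decision rule, so that goes further than the text.

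**Conclusion.** The inconsistency is real: A60 and A62 use different alphas for the between-diet strength t test in Part B, and 9 per group does not give the stated 80% once the correction in A62 applies. Power is about 69% for the two post-exercise times, 63% with baseline added and 58% for two times on two machines. These figures rest on an effect solved from A60's own 80% with an independent t test and 9 completers per group. The drop below 80% holds for any divisor of two or more; its exact size depends on a divisor and an SD that the protocol does not state. No arithmetic within A60 is shown to be wrong.

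**What to change.** Use one alpha in both answers, by either route and without adding participants.

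1. State in A62 how many strength comparisons are corrected for, and restate in A60 the power of 9 per group at that alpha. The stated power becomes less favourable: about 69%, 63% or 58% for two, three or four comparisons, all else as in A60.
2. Name in both A60 and A62 the one strength comparison (time point and machine) that Part B is sized on, test it at two-sided 0.05, and apply the Bonferroni correction to the remaining comparisons. The 80% can then stay as far as alpha is concerned, but one time and one machine must be chosen before any data are seen.

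Either route takes a sentence or two in each answer. The wording of the dependent t test in A60 needs its own correction, and any restated power should be computed after that has been settled.
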